## Abstract

**Background:**

One of the greatest barriers found by physical therapy treating individuals with Parkinson’s disease (PD) is the adherence to treatment, associated with the lack of motivation to remain active. Therefore, there is a need to change the look given to physical therapy and for the individual, seeking the centralization of the therapy in their preferences. This study aims to present the EMPOWER-PD, a protocol based on individual preferences and its design for feasibility.

**Method:**

A 12-week pilot for a randomized clinical trial will assess the feasibility and preliminary effectiveness of the EMPOWER-PD and make comparisons with conventional physical therapy (CPh). Both protocols consist of mobility and locomotion training, and aim at improving motor and non-motor symptoms through different approaches. The EMPOWER-PD aims to provide a source of motivation and empowerment of health through the self-knowledge of the individual’s abilities and limitations, in a protocol that addresses individual preferences. The CPh is based only on physiotherapist decisions, not addressing the individual’s preferences or motivation/empowerment. The target recruitment will be 24 PD individuals, between stages I and III of Hoehn and Yahr (HY), who will be recruited from Brazilian Parkinson’s disease Rehabilitation Initiative (BPaRkI) with allocation ratio 1:1. A computerized block randomization procedure will be implemented by a blinded researcher with the participants blinded to group assignment. The sessions will be conducted in a group setting, twice a week, during 60 min for 8 weeks, followed by 4 weeks of follow-up. The primary outcomes will be the feasibility data (adherence, recruitment rate, and safety). The secondary outcomes will assess the preliminary efficacy on qualitative assessment about individual’s motivation/empowerment and quantitative motor outcomes (Timed Up and Go and Dynamic Gait Index) and non-motor symptoms (6-min walk test and Fatigue Severity Scale). The recommendation to have 6–12 participants per group will be adopted based on the qualitative analysis to the sample size.

**Discussion:**

This study will provide important insights about the physical therapy approach in PD individuals. The EMPOWER-PD is innovative because (1) it proposes an intervention that includes an individual-centered approach with motor control principles; (2) it aims to provide a source of motivation and empowerment of health; (3) assesses the individual in a global view considering motor and non-motor symptoms, using both, qualitative and quantitative metrics.

**Trial registration:**

RBR-7ZBXQ5

**Electronic supplementary material:**

The online version of this article (10.1186/s40814-019-0394-9) contains supplementary material, which is available to authorized users.

## Background

The global benefits of physical therapy in the domains of International Classification of Functioning, Disability and Health (ICF) [1] in activity, participation, and body structure and function for individuals with Parkinson’s disease (PD) have been clearly established in the literature [2, 3]. However, studies have shown that some individuals present with barriers to the practice of physical therapy, decreasing their motivation towards the treatment and consequently decreasing their adherence [4–6]. Among the strategies suggested both by PD individual’s and by the therapists to engage the individuals in the exercise, a joint work seeking to stimulate self-efficacy and confidence, recognizing and respecting their barriers and individual motivations, were considered of utmost importance [7].

New approaches recommended targeting these challenges include employing the use of individual-centered care [2]. The individual-centered care aims to provide respectful and responsive care to their individual preferences, their needs, and values, ensuring that they guide all clinical decisions [8–10]. The focus is accessing the “person behind the disease,” respecting their preferences and ensuring their inclusion in the choices of their treatment through active participation, enabling them to develop responsibility for their self-care [10]. This integration of the subject with their rehabilitation promotes the possibility of self-reflection, prioritization, and application of problem solving skills related to performance issues in the domains of activity and participation, developing self-care and autonomy [2, 11].

This new approach of physical therapy could guide the individual towards the empowerment of their own health, establishing the promotion of an intrinsic motivation by encouraging behavioral change [12] and thus, could increase the adherence to treatment and decrease the need for constant professional supervision for one to remain active. However, there are no intervention protocols that currently integrate conventional physical therapy (CPh) with this new approach of quality of care that includes the individual in the clinical decision to motivate and develop an empowerment of their own health.

Based on all information above, this study presents the EMPOWER-PD protocol, a physical therapy approach based on the individual preferences. As a new intervention protocol, it is necessary to verify it feasibility when applied to the target population. This study presents the design of the feasibility randomized controlled trial that aims to(i)Investigate the feasibility of the EMPOWER-PD protocol through adherence rate, recruitment rate, and safety.(ii)Compare the preliminary effectiveness of the EMPOWER-PD with the conventional physical therapy through qualitative analysis of motivation, empowerment of health, followed by the analysis of the dependency of professional supervision by individuals to remain active in the post follow-up period.(iii)Compare the preliminary effectiveness of the EMPOWER-PD in motor and non-motor symptoms (functional mobility, gait, fatigue, aerobic capacity/endurance) with the conventional physical therapy through quantitative analysis of estimates of 95% confident interval.

We hypothesize that the EMPOWER-PD will lead to higher adherence and safety when compared with conventional physical therapy. Concerning motivation, health empowerment and dependency of professional supervision by individuals to remain active in the post follow-up period, we hypothesize that the EMPOWER-PD will be associated with better outcomes in preliminary effectiveness than the conventional physical therapy. For the motor and non-motor symptoms, we hypothesize that the EMPOWER-PD will be associated with similar preliminary effectiveness to the conventional physical therapy.

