#### Sample size

The primary outcome of this pilot for a randomized clinical trial will be the feasibility (adherence, recruitment rates and safety). As in feasibility studies a formal sample size calculation is not required [30], we estimated the number of participants based on qualitative analysis. We will adopt the recruitment of 6–12 participants per group as a recommended for qualitative studies, being adopted the major value (*n* = 12 per group) [31]. Accordingly, we will use the criteria of sampling saturation that means “collecting data until no new information is obtained” [32].

In relation to the quantitative variables, the present study is not intended to be fully powered for detection of statistically significant effects, but it will enable a sample size calculation related to the quantitative variables for a future randomized trial [33]. For that, we plan to select the sample size based on reasonable precision of estimates of standard deviation of quantitative measures which have shown sensitivity in this feasibility study.

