#### Randomization

A computerized block randomization procedure will be implemented by a blind researcher. Individuals with PD will be randomly allocated to two arms: (a) EMPOWER-PD or (b) conventional physical therapy (CPh). An independent person will notify the treating physiotherapists by email to ensure concealed allocation. The distribution of the groups will be kept in a closed envelope. The allocation will be on an equal ratio (1:1) between the two groups of interventions, stratifying by sex and by the stages I–III of Hoehn and Yahr scale (HY) [34]. To avoid bias, blinded testers will assess the participants.

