### Data management and analysis

For the feasibility analysis, the results will be expressed as percentage and numbers referring to adherence, recruitment rates, and safety, respectively. After qualitative data collection, two authors will perform the total transcription of the audios and notes line-by-line. Then, two authors will start the codification of the *corpus.* After transcription, the corpus will be codified in numbers and their respective groups (e.g., # ID1emp, # ID5cph) by a blinded third researcher, for the later analysis by a fourth researcher. Codes will then be consolidated into categories after an extensive exploration of the material and interpretation of the data obtained according to thematic analysis of the content. From this, entire research team will discuss to formulate inferences.

To verify the preliminary effectiveness regarding quantitative outcomes, the descriptive analysis will be performed with frequency, central tendency, and variability (mean and standard deviation or median and interquartile interval) in the statistical program SPSS 20.0 for Windows (IBM-USA). All results of the preliminary efficacy of the feasibility trial will be described as estimates of 95% confidence interval. An intention-to-treat analysis will be done with participants including who eventually will be missed in any part of the study.

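### The hypothesis of similar motor and non-motor effects has no margin, and a 95% interval of about ±0.85 SD at 12 per arm cannot support it

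*Protocol article*

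**What the plan says.** Aim (iii) in the Background of the protocol article is to compare EMPOWER-PD on functional mobility, gait, fatigue and endurance "with the conventional physical therapy through quantitative analysis of estimates of 95% confident interval". The hypothesis paragraph that follows adds: "For the motor and non-motor symptoms, we hypothesize that the EMPOWER-PD will be associated with similar preliminary effectiveness to the conventional physical therapy". The article gives no margin, for any outcome, that would define similar.

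Under Data management and analysis, "the descriptive analysis will be performed with frequency, central tendency, and variability" (mean and SD, or median and interquartile range). The section continues: "All results of the preliminary efficacy of the feasibility trial will be described as estimates of 95% confidence interval". It does not say whether the interval is for each arm or for the difference between arms.

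On size, the abstract states: "The target recruitment will be 24 PD individuals", allocated 1:1. The Sample size section takes 12 per group from a recommendation for qualitative studies and adds that "the present study is not intended to be fully powered for detection of statistically significant effects". Randomization is planned "stratifying by sex and by the stages I–III of Hoehn and Yahr scale".

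**The concern.** A hypothesis that two treatments are similar has content only once someone says how large a difference would contradict it. Without a margin, no result can clearly support or refute it. The hypothesis and its standard of judgement belong in the protocol, so this is not a detail that can simply be left to a statistical analysis plan.

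The gap matters here because the intervals for TUG, DGI, FSS and 6MWT will be wide. A wide interval will usually include zero whether the arms are alike or one is moderately worse. With similar as the expectation written in advance, and nothing to say how the interval bears on it, an inconclusive pilot could be taken as agreeing with its hypothesis. That impression could then carry over into the definitive trial that the Discussion foresees.

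**Working it through.** **Inputs from the article.** 12 per arm, 1:1, and a 95% confidence level (Sample size; Randomization; Data management and analysis). The plan's own figure reproduces: 2 × 12 = 24. There is no power or precision calculation to reproduce.

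**Assumptions.** The article gives no SD, effect size, margin or baseline correlation. Everything below is therefore in units of the outcome SD, with approximately normal outcomes and equal variances. The true deficits and correlations are illustrative ranges.

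**1. Width of the unadjusted interval for the difference.**
Half-width = t(0.975, 22) × √(2/12) = 2.074 × 0.408 = 0.85 SD.
The retention criterion is > 80%, and 0.8 × 12 = 9.6. With about 10 evaluable per arm, the half-width is 0.94 SD.

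**2. How often the interval includes zero when EMPOWER-PD is truly worse by d SD.** This uses the non-central t with 22 df and non-centrality d / √(2/12).

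| True deficit (SD) | Interval includes zero |
|---|---|
| 0.3 | 89% |
| 0.5 | 78% |
| 0.8 | 53% |
| 1.0 | 35% |
| 1.2 | 20% |

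A deficit of about 1.2 SD is needed before zero is excluded in 80% of trials. With 10 per arm, the figure at 0.5 SD is 81%.

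**3. If the interval is given for each arm separately.** The two arm intervals overlap in about 95% of simulated trials under a true deficit of 0.5 SD. It therefore matters which interval is meant.

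**4. What a margin would demand.** An interval 2 × 0.85 = 1.70 SD wide cannot fit inside any symmetric margin narrower than ±0.85 SD (in observed SD units). For the one-sided question alone, with no true difference, the chance that 12 per arm excludes a 0.5 SD deficit is Φ(0.5/0.408 − 1.96) ≈ 23%. For a future trial, n per arm = 2 × (1.960 + 0.842)² / margin² (one-sided 0.025, 80% power, true difference zero):
- margin 0.3 SD: 175
- margin 0.5 SD: 63
- margin 0.8 SD: 25

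**5. What baseline adjustment would gain.** Half-width ≈ t × √(2/12) × √(1 − r²), where r is the assumed correlation between baseline and follow-up. Adjusting for baseline only leaves 21 df; adding sex and three HY stages costs 3 more, leaving 18.

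| r | Half-width, 21 df | Half-width, 18 df | Includes zero at 0.5 SD deficit (21 df) |
|---|---|---|---|
| 0.5 | 0.74 | 0.74 | 73% |
| 0.7 | 0.61 | 0.61 | 63% |
| 0.8 | 0.51 | 0.51 | 50% |

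The formula leaves out the small variance cost of chance covariate imbalance, so these gains are slightly optimistic. Adjustment narrows the interval but does not by itself make similarity demonstrable.

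**The case against.** The strongest reply is that this is a declared pilot. The Sample size section says openly that the study is not powered for these outcomes and that they serve to size a later trial. TUG, DGI, FSS and 6MWT are secondary, and the thresholds for going on to a larger trial (Primary outcomes section) concern only recruitment, retention and adverse events. Aim (iii) is already an estimation aim, and the disputed sentence is an expectation about preliminary effectiveness, not a formal equivalence objective. All of this stands. Wide intervals at 12 per arm are no error.

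A reader might go further and infer that the trial will report similarity whenever an interval includes zero or the arm intervals overlap. The article contains no such rule. The 78% is the chance of an inconclusive interval, not of a false claim. A ±0.85 SD interval that is properly read shows its own imprecision.

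A reader might also infer that the comparison will ignore baseline values and the stratification factors. The article names no model and no covariates. That is silence which a fuller analysis plan may fill, so it is not a defect, and the gain from adjustment depends on correlations that the article does not give.

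What the reply does not answer is that similar is hypothesized without a definition, in a design whose intervals cannot bear on it, and that nothing in the article says an interval including zero should not be taken as support.

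**Conclusion.** The point holds as a defect in how the hypothesis is stated. Similar effectiveness has no margin, and at 12 per arm the unadjusted 95% interval of about ±0.85 SD cannot tell similarity from a moderate deficit. The arithmetic for the width rests only on the stated sample size and confidence level. The 78% also needs the illustrative 0.5 SD deficit, and the range is 89% to 53% for deficits of 0.3 to 0.8 SD. The documents do not support calling the pilot underpowered for its purpose, asking for more participants, or saying that a false claim of similarity is planned. The matter is worth correcting because the correction is cheap and settles what the trial may conclude about these outcomes.

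**What to change.** 1. **Background, hypotheses.** Replace the similarity hypothesis for motor and non-motor outcomes with an estimation aim. For example: *For TUG, DGI, FSS and 6MWT we will estimate the difference between EMPOWER-PD and CPh, without a hypothesis of similarity.*
2. **Data management and analysis.** State that the 95% interval is for the between-arm difference at weeks 8 and 12. Preferably take it from a model adjusted for the outcome's baseline value and, if the small sample allows, for sex and HY stage.
3. **Same section.** Add one sentence saying that an interval including zero is not evidence of similarity.
4. **Only if similarity is to be claimed.** Name a margin for each outcome before the arms are compared, with its justification, and claim similarity only if the interval lies inside it. At 12 per arm this is realistic only for very wide margins, so its natural place is the definitive trial.

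The cost is the wording of a few sentences, a weaker stated conclusion, and a few degrees of freedom (one for baseline, three more for sex and HY stage). No extra participants or visits are needed.

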## Methods

### Idealization and development of the EMPOWER-PD

The idealization of EMPOWER-PD arose from the observation of the reality of the PD individuals and physiotherapists of the Brazilian Parkinson’s disease Rehabilitation Initiative (BPaRkI) (Florianópolis/Brazil). When the BPaRkI participants would return from a recess of activities (about 2 months), motor symptoms were always found to be worse than before. However, they would improve during the course of the treatment. We hypothesized that this was not purely the natural progression of the disease, but the physical inactivity and the lack of self-care in the absence of professional supervision. From these observations, three major facts were pointed out: the first is how the individual’s dependence on the professional delays their rehabilitation process; and the second is how we as professionals were corroborating for the increase and maintenance of this dependency. Another fact is that most of the participants of the BPaRkI came by medical recommendation with the diagnosis of the disease. This could explain in part their passivity towards their state of health and the reason why they are there.

Therefore, we began the search for a reality where the therapist succeeds in helping the subjects to help themselves. The concept of the centralization of the individual, as described by the gold standard guide of physical therapy in PD [2], was the central focus of the EMPOWER-PD. The purpose of this protocol is not the mere reproduction of the exercises in different individuals with PD, but rather the adaptation of the protocol to the actual needs and preferences of different groups of individuals. With this in mind, as a first step, we started listening to the BPaRkI participants. We created focus groups to identify preferences in leisure, expectations, exercise practice, pleasure, motivation, and daily routine. This can be considered as the most important step of the protocol, as it is very important to stimulate active participation in their state of health [9, 10, 13] and increase motivation.

Adding this information with the literature about the proven benefits of the physical therapy in PD [2, 3, 14–19], we started the development of EMPOWER-PD based on a mobility and locomotion training, as gait is considered one of the most potent indicators of disability in PD [20–22]. The protocol aims to provide a source of motivation and empowerment guiding the individual along this path through four goals. The first is the self-knowledge (first and second weeks) of their body through self-monitoring and self-management [2, 5, 8, 11, 23], where the individual reconnects body and mind with self-care [24]. In the second goal (third and fourth weeks), the individual approaches motor strategies during daily activities and during challenging exercises/situations. From this, the individual improves their ability to exercise [11, 25]. The third goal (fifth and sixth weeks) is focused on the stimulation of courage and confidence in their perceptions and convictions of how far they can care of themselves respecting their limits and their safety [23, 25]. In the fourth goal (seventh and eighth weeks), “the therapist moves away,” and the individuals choose their own exercises based on their preferences and on what they have achieved in the earlier weeks [5, 26]. The fourth goal seeks to provide an experience of independent self-care doing activities that are pleasurable and with people who have gone through the same process and that are equal to them regardless of the stage of the disease [2, 10, 26]. It should be noted that during all goals of intervention, the individual chooses the exercise intensity. For more details, see Table 1.

**Table 1 Tab1:** EMPOWER-PD. 8-week physical therapy protocol, twice a week

Weeks/goals	Objective	Exercise	Instructions	Progression
First–second Self-knowledge	Stimulate self-knowledge: how does my body behave in the task?	From sitting, get up, and walk in an 8-m track, make the turn to the “U” (1 m), and walk diagonally to sit on the next chair.	Attentional focus during the task: pay attention to how you lift and sit, to the length and width of the pitch, arm swing and trunk movement, and their breathing, respectively.	The “U” will decrease (1 m–80 cm pivot) as well as the height of the chair (50 cm–45 cm–40 cm). Self-controlled speed.
Third–fourth Developing strategies for limitations and improving skills	Develop own strategies to overcome limitations (internal cues, imagery, sound stimuli, body adjustments). Enhance skills through their preferences.	From sitting, get up and walk in an 8-m track (passing and skirting obstacles, passing through narrow spaces (60 cm), holding objects) to the “U” (80 cm), interact with their preference, turn around, and sit on the next chair.	Attentional focus during the task: pay attention to how you go through the challenges. Realize where you have easy and difficulty. Test with your body the ways for you to overcome the difficulty and enhance what you have easily.	The “U” will decrease (80 cm–60 cm pivot) and the height of the chair (45 cm–40 cm bench). Obstacles will grow taller and narrower; the spaces will rise to 50 cm, and they will exchange objects between them during the gait.
Fifth–sixth Flexibilizing and developing confidence	Develop confidence and new strategies during walking and mobility in conflicting situations of daily living.	From sitting, get up, and walk 8 m under the same challenges of the previous week, but under more conflicting stimuli (talk to the duo during the task, different speeds, stop abruptly, traffic signal, sing, perform their concomitant preferences the task).	Attentional focus during the task: pay attention to how your body behaves in these conflicting situations. Test the strategies you already know and realize how safe you are by doing the task. Keep challenging yourself while always prioritizing your safety.	Pivot in all the ends and the height of the chair will continue of 45 cm–40 cm bench.
Seventh–eighth Winning autonomy and power for an active life	Decrease dependence on the therapist. Develop your own therapy based on your choices.	Booklet with the image of the circuit available for the free will to choose their exercises, their intensity, participants per season, and moment of progression.	As a team, choose how you guys will set up your circuit. I will be here to help you and listen to your doubts. Remember to respect your body and safety, but always progress using your individual strategies. Have fun!	At this stage, the therapist will be co-adjuvant in therapy, always stimulating the confidence and tranquility of the group and appearing in a few moments.

Legend: *m* meters; *cm* centimeters

One of the peculiarities of the EMPOWER-PD is the possibility to expand the learning with other participants in group. We believe that this is a very special aspect of this protocol because it provides benefits to both activity and participation [27]. As previously mentioned, the EMPOWER-PD comes as a new approach for individuals with PD and for the physiotherapists involved in this process. During the development of this protocol, we also seek to a new way of acting as a therapist. In this case, there could not be space for hierarchy and differences [7, 9, 12], since the re-encounter with health is in all people involved. As knowledge is shared either through professional expertise or through the experience of living with PD, it must be kept in mind that we are all “people” behind the role of therapist and patient and this is also what EMPOWER-PD seeks to put into focus.

